### Handling missing data

Where a given outcome is measured at two or more time points, missing post-randomisation assessments will be dealt with by fitting linear mixed models to all the available measures using maximum likelihood methods. Such an approach provides valid inferences under the assumption that the missing data mechanism is ignorable (or Missing at Random). If post-randomisation variables are found to be predictive of the dropout rate, multiple imputation will be considered using *K*-nearest neighbours.

### Economic evaluation

Cost data is usually skew but will be analysed using arithmetic means so that total costs are preserved. Non-normality in errors will be allowed for by using generalised linear models with an appropriate error structure (for example, a gamma distribution
[12]). Incremental cost-effectiveness ratios or an incremental cost-utility ratio will be presented where appropriate. Cost-effectiveness acceptability curves will be plotted to summarise the uncertainty in cost-effectiveness.

### Detailed study plan

#### Selection of subjects

The local transplant clinic database will be used to identify patients meeting the baseline inclusion and exclusion criteria. At the start of the trial, the entire population of transplant clinic attendees who meet the eligibility criteria are potentially eligible for recruitment. On subsequent screening rounds, patients who reach 12 months post-transplantation after the start of the trial will become eligible and these will be recruited before the next screening round.

#### Informed consent

Potentially eligible patients will be approached at a routine clinic appointment by the principal investigator (PI) or research nurses and given printed and verbal information about the trial. They will have the opportunity to return for a second consultation within a few days to give informed consent for recruitment into the study or to do this on their next routine appointment. Alternatively, eligible patients will be sent information about the study through the post, for discussion and consent at their next routine appointment. Following consent, full eligibility criteria will be reviewed. This may include testing for chronic viral diseases (if they have not been tested within the last 5 years) and pregnancy (if a patient’s history suggests there is the possibility of pregnancy).

#### Inclusion criteria

• Sufficient grasp of English language to give written and witnessed informed consent to participate

• Renal transplant recipients >1 year post-transplantation, male or female

• Aged 18 to 70 years

• Estimated glomerular filtration rate (eGFR) ≥ 30, based on the four-variable Modification of Diet in Renal Disease (MDRD) approach

#### Exclusion criteria

• Recipient requiring HLA desensitisation to remove antibodies for a positive cross-match transplant

• Recipient known already to have HLA antibodies who has received specific intervention for those antibodies or for CR

• Recipient of an additional solid organ transplant (for example, pancreas, heart, etc.)

• History of malignancy in previous 5 years (excluding non-melanomatous tumours limited to the skin)

• Positive for hepatitis B surface antigens, hepatitis B core antibodies, hepatitis C or HIV (according to a test performed within the previous 5 years)

• History of acute rejection requiring escalation of immunosuppression in the 6 months prior to screening

• Patient enrolled in any other study involving administration of another investigational medical product (IMP) at time of recruitment

The following exclusion criteria are based on the summaries of the product characteristics of the IMPs:

• History of an ongoing or previous infection (no time limit) that would prevent optimisation of immunosuppression, including ocular herpes simplex

• Known hypersensitivity to any of the IMPs

• Known hereditary disorders of carbohydrate metabolism

• Pregnancy or breastfeeding females (based on verbal history of recipient)

• Pre-menopausal females who refuse to consent to using suitable methods of contraception throughout the trial

### Randomisation procedure and code break

Prior to randomisation but after consent, site staff will register a recruit on the web-based electronic data capture system (InferMed MACRO), hosted at the King’s Clinical Trials Unit (KCTU). Each will be assigned a unique study patient identification number (PIN) by the system. Samples from all recruits will be sent to the HLA laboratory, along with this PIN and a sample request form containing other information required for randomisation.

Laboratory staff will screen for HLA Ab and perform SAB testing on positive screening samples to check for the presence of DSA. Once this information is known, the lab staff will access the KCTU randomisation system and randomise the patient, using the HLA Ab results. Randomisation will be further stratified by centre and current immunosuppression. The lab staff, PIs and nurses at the site will be automatically emailed and the randomisation system will inform them whether the patient is in a blinded or unblinded group. If the patient is in an unblinded group, the system will inform the PI of the HLA Ab status. Unblinded patients will be identified by blue stickers appended to the notes and all future clinical samples. The system will tell the trial staff to enter HLA Ab– patients into the subsequent 8-monthly screening rounds, and also whether the patients have been selected to provide future samples for the 4-monthly scientific analysis (for transfer to the chief investigator’s laboratory). This information will be relayed using a star on the blue labels that are appended to the laboratory request forms.

The notes and samples from blinded patients will have green stickers and labels. The HLA Ab status will not be given to the PIs or trial staff. A star will be used to tell the trial staff which recruits have been selected to provide 4-monthly samples for transfer back to the chief investigator’s lab for scientific analysis. These patients will have samples taken every 8 months for HLA Ab screening. Once inside the lab, the lab staff will use their knowledge of the HLA status to determine which HLA Ab– patients will undergo screening. The samples from HLA Ab + patients will be discarded.

On the second and subsequent HLA Ab screening rounds, the lab staff will update the randomisation system. The results from patients in the unblinded groups only will be forwarded to the PI and laboratory staff via email. This will indicate whether the status has changed, which will trigger the change in the treatment protocol for those that have changed from HLA Ab negative to positive.

Laboratory staff at each recruiting site, with access to HLA Ab results, will be provided with a unique username and password to access the randomisation system. Password access must be authorised by the trial manager in all cases and direct requests from sites will not be processed. Access to the system is via the internet
[13] by clicking the ‘randomisation – advanced’ link and selecting the OuTSMART Trial.

There are no blinded study medications in the trial so no emergency code break is required. In the event that a study site clinician wishes to be made aware of blinded laboratory results, this must be discussed and agreed with the trial manager and the chief investigator in all cases. It is not anticipated that unblinding in this manner will be required and only in extraordinary circumstances would this be agreed.

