1) will know their HLA Ab status and will be offered treatment. HLA Ab– patients will remain on their existing immunotherapy and randomised 1:1 into either the blinded (C) or unblinded group (D), with only the latter knowing their HLA Ab status. Both these groups will receive regular Ab status monitoring for the first 3 years. Those patients who become positive during subsequent screening rounds (approximately 10% per year) will be moved to the appropriate HLA Ab + groups (DSA + or non-DSA+) for final data analysis. All patients in group D found to be positive on the second or subsequent rounds will be offered the same treatment as those patients who were positive in the first screening round, and followed up for 3 additional years from the time they become positive. Thus, the maximum amount of time any single patient can remain in the study is 6 years. ‘New’ patients, randomised but initially HLA negative at baseline, will be included in the intended primary analysis of HLA positive groups at each successive 8 monthly screening round. The patient flow diagram according to CONSORT guidelines is provided as Figure 
2.

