
### Laboratory tests

#### Human leukocyte antigen antibody analysis

Serum prepared from 10 mL of blood will be used in the commercially available LABScreen tests (One Lambda, Canoga Park, CA), containing fluorescently tagged beads coated with purified HLA antigens. All participating centres have Luminex equipment (Luminex Corp, Austin, Texas) for analysis of these tests and the skills to process samples and interpret results. Therefore, the tests will be performed in each of the centres. A sequential analysis of samples is planned, first to identify those with HLA Ab, using mixed class I and class II Ab screening beads coated with multiple different types of HLA. The manufacturer’s definition of positive and negative tests will be used when interpreting the results. In those patients with positive results, the specificity of the HLA Ab will be determined by SAB, coated with single HLA class I or class II antigens. As before, when interpreting the results, the manufacturer’s definition of positive and negative tests will be used. Any patient with a positive test for HLA Ab identified by SAB will be regarded as HLA Ab + for the trial if the mean fluorescence intensity (MFI) is ≥2,000. If the HLA Ab are directed against a mismatched donor HLA antigen, the patient will be assigned as DSA+. The number of DSA with MFI ≥ 2,000 will be used to define the Ab ‘burden’ of an individual. In the final analysis, correlations between HLA Ab burden and outcomes will be sought. Patients with SAB positivity that is difficult to label as DSA + or non-DSA + (because of insufficient data on donor mismatches, for instance), will be regarded as being non-DSA+. Patients with a positive reaction on screening but lacking reactivity with the SAB at the level described will be considered negative. Excess serum will be stored. The same screening will be undertaken for HLA Ab– patients every 8 months, with the samples taken at a routine clinic appointment.

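### At re-screening, laboratory staff who know the arm decide which converters enter the primary comparison

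*Protocol article*

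**What the plan says.** **Baseline.** Under Randomisation procedure and code break, the laboratory first tests for HLA antibodies and DSA. Then: "Once this information is known, the lab staff will access the KCTU randomisation system and randomise the patient, using the HLA Ab results". The classification therefore precedes allocation.

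**After allocation.** The same section then has the laboratory told the arm, blinded or unblinded: "The lab staff, PIs and nurses at the site will be automatically emailed and the randomisation system will inform them whether the patient is" (the sentence ends by naming the group). It adds, "Unblinded patients will be identified by blue stickers appended to the notes and all future clinical samples", and for the other arm, "The notes and samples from blinded patients will have green stickers and labels". The blue labels also go on laboratory request forms.

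**Re-screening.** The laboratory selects the samples: "Once inside the lab, the lab staff will use their knowledge of the HLA status to determine which" antibody-negative patients are tested. It then enters the outcome: "On the second and subsequent HLA Ab screening rounds, the lab staff will update the randomisation system". Results for the unblinded arm only are emailed to the principal investigator and to laboratory staff, and a change to positive triggers the treatment protocol.

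**Consequence for the analysis.** Under Trial design, patients who turn positive "will be moved to the appropriate HLA Ab + groups (DSA + or non-DSA+) for final data analysis". Sample size calculations counts them in groups A and B, that is, in hypotheses 1.1 and 1.2. Primary end points resets their time zero to the positive test and extends their follow-up.

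**Assay rules.** Under Human leukocyte antigen antibody analysis, testing is done in each centre. Positivity follows the manufacturer's definition at the screening and single-antigen steps, plus an MFI of at least 2,000. A default covers ambiguous cases: "Patients with SAB positivity that is difficult to label as DSA + or non-DSA"+ count as non-DSA+.

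**The concern.** Converters enter the primary comparison through a call made after randomisation by people who know the arm. If near-threshold or ambiguous results were called differently in blue and green samples, the antibody-positive groups would differ in underlying risk before any treatment effect. Analysing by allocated arm does not repair this, because membership of the analysed set is what has been selected.

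The call also has different consequences in the two arms. In both arms a positive result moves the patient to a positive group, resets time zero and extends follow-up. Only in the unblinded arm does it also bring an offer of treatment, so staff there may have a reason to be more ready, or more reluctant, to call a positive.

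**Working it through.** **1. Who knows what, and when**

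| | Baseline | Re-screening |
|---|---|---|
| Arm known to the laboratory when the sample is read | No: result first, then randomisation | Yes: earlier email and coloured labels |
| Who classifies | Local laboratory | Local laboratory |
| Effect of a positive call | Sets the stratum before allocation | Admits the patient to the primary comparison; triggers treatment in the unblinded arm only |

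No section masks the laboratory to the arm. Blinding in this protocol means that clinicians and patients in the standard-care arm do not know the antibody result.

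**2. The plan's sample sizes**

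These reproduce with the arcsine formula n = 2(z₀.₉₇₅ + z₀.₈₀)²/h², where h = 2·arcsin√p₁ − 2·arcsin√p₂. For 30% v 16%, n = 138.8, rounded up to 139. For 16% v 6%, n = 145.8, rounded up to 146. Neither depends on who reads the samples.

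**3. Share of the antibody-positive set that enters through this call**

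Inputs from Sample size calculations: 2,522 enrolled, 25-30% positive at baseline, 6% of negatives converting and 2% dropping out per round. Each round multiplies every group by 0.98 and then moves 6% of the negatives. Both arms together:

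| Baseline prevalence | Re-screens | Baseline positives | Converters | Converter share |
|---|---|---|---|---|
| 25% | 3 | 593 | 302 | 34% |
| 25% | 4 | 582 | 383 | 40% |
| 30% | 3 | 712 | 281 | 28% |
| 30% | 4 | 698 | 357 | 34% |

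The plan's final mix (13% DSA+ and 27% non-DSA+, so 40% positive) gives (40 − 25)/40 = 37.5% and (40 − 30)/40 = 25%.

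The target of 950 negatives per arm (Expected duration of trial), with four rounds, gives 57 + 53 + 48 + 45 ≈ 202 converters per arm, the negatives shrinking by 0.94 × 0.98 each round. Baseline positives per arm are (2,522 − 1,900)/2 = 311. The share is 202/513 = 39%, near the top of the range.

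Overall: about 25-40%.

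**4. Possible effect (assumed, not in the documents)**

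Suppose that treatment does nothing and that the unblinded arm alone over-calls 10% of its converters, all of whom fail at the negative-group rate of 6%. That adds about 20 patients, 20/513 = 3.9% of the positive group, spread evenly over the two subgroups.

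- Non-DSA: (16 + 0.039 × 6)/1.039 = 15.6%, a shift of 0.4 points against a planned difference of 10.
- DSA: (30 + 0.039 × 6)/1.039 = 29.1%, a shift of 0.9 points against a planned difference of 14 (0.9/14 ≈ 6%).

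The reverse habit, leaving out the same number of such patients in the unblinded arm, gives (16 − 0.039 × 6)/0.961 = 16.4% and (30 − 0.039 × 6)/0.961 = 31.0%, a bias against the intervention.

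For the non-DSA test, a slightly larger excess of 5% raises the two-sided type I error from 5.0% to about 5.2% at 146 per group, or 5.3% at 282 per group (27% of 1,043). An excess concentrated in one subgroup would shift that subgroup more.

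**5. Hypothesis 2**

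It compares all randomised patients whatever their antibody status, so this call does not select its population.

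**The case against.** The strongest reply is that little is left to judge. Results are read on Luminex equipment, the manufacturer's definition applies at both steps, and the MFI cut-off is numeric. Screen-positive samples without that single-antigen reactivity count as negative. Recipient and donor HLA types are baseline data, and hard-to-label cases default to non-DSA+, which stops ambiguity drifting into the DSA group. Laboratory staff have no stated role in treatment or outcome assessment, and no stated motive to favour either arm.

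Most of this stands, and it is why the plausible effect is small. It does not close the gap. Near-threshold readings still have to be handled. Donor type is recorded only if known, so matching a specificity to a donor mismatch can take judgement. The default operates only once someone has declared a case ambiguous.

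A second reply is that the green label may serve to tell a local laboratory which results to withhold from clinicians. The document does not state this purpose, but it is reasonable, and the fix must replace that function.

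Four stronger readings are tempting and are not supported:

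- That the whole primary population is judged unmasked. Baseline positives, the majority, are classified before allocation.
- That 10% extra weak positives across the whole positive group is a mild scenario. It gives 15.1% and 27.8%, the latter a 2.2-point false benefit, or 16% of the planned 14. But it needs about 51 extra positives per arm, roughly a 25% over-call among the 202 converters.
- That a positive call has no consequence in the blinded arm. It changes group, time zero and follow-up; only treatment is unchanged.
- That hypothesis 2 is compromised in the same way. Its population is not selected here; the only link is that it is tested after a significant superiority result.

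**Conclusion.** The point holds for converters at re-screening. The article specifies arm notification and arm-coloured samples for the staff who make the call, so this is a stated procedure and not a detail left to a fuller document. About 25-40% of the antibody-positive set passes through it, depending on baseline prevalence and number of rounds.

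The documents contain no evidence of bias, and its direction is unknown. Under the assumed 10% miscall among converters, the shift is about 0.4 points (non-DSA) or up to about 1 point (DSA), in either direction. That figure rests on the assumed miscall rate, the 6% failure rate for the miscalled patients and an even spread over subgroups. This is an inexpensive improvement that removes an avoidable doubt. It does not show that the primary comparison is invalid.

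**What to change.** Amend Randomisation procedure and code break as follows.

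1. Remove laboratory staff from the allocation email and from the later email of unblinded-arm results. If the second email stays, masking is lost after the first re-screen.
2. Let the randomisation system show laboratory staff only 'randomised' and 'test / do not test'. They need antibody status to select samples, but not the arm.
3. Put neutral labels bearing only the patient identification number on HLA samples and request forms. Keep blue and green for the notes.
4. Have the laboratory lock the re-screening result (negative, non-DSA+ or DSA+, with MFI) before the system uses the arm to decide whether to notify the principal investigator. The system already forwards later results by arm.
5. State that no trial HLA result leaves the laboratory except through the system, because the green label can no longer flag results to withhold.

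The cost is a change to notification templates and labels, and re-training of five laboratories. No extra tests are needed, and 139 and 146 per group stand.

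As a supporting check, repeat the primary comparison in baseline positives only, who were classified before allocation. It cannot replace the primary analysis: with about one third DSA+, 311 baseline positives per arm give about 104 in the DSA groups before dropout, short of 139.

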### Trial medication

All treatments will be introduced on the basis that they will be tailored to the individual patient, according to compliance, tolerance and achievement of target levels (for tac). Failure to tolerate one or more of the components of the protocol (or refusal to take any of the agents) will not be used as a reason for withdrawal from the study.

#### Investigational medical products and dosing regimen

The optimised treatment protocol in the two groups (B1 and B2 in Figure 
1) with HLA Ab will be:

• Mycophenolate mofetil twice, three times or four times per day, or enteric-coated mycophenolic acid twice per day, with the daily dose determined according to local unit guidelines. The patient will be stabilised on the maximum tolerated dose.

• Tacrolimus once or twice per day, according to local unit preference, with dose titrated to achieve 12-hour post-dose levels of 4 μg/L to 8 μg/L (4 ng/mL to 8 ng/mL). The patient will be stabilised on the maximum tolerated dose that achieves these levels.

• Prednisolone once per day. Starting at 20 mg for two weeks, then reducing by 5 mg once per day every two weeks down to their previous maintenance dose or 5 mg once per day.

After consultation with the Medicines and Healthcare products Regulatory Agency (MHRA), we have confirmed that all these medicines will be classed as IMPs, whereas all others will not. Mycophenolate mofetil/mycophenolic acid is being used outside of its marketing authorisation (which states that it should be used with ciclosporin). However, because it is now used widely in combination with tacrolimus in most units in the UK, the two can be regarded as standard care. We therefore propose that the three drugs will not require labelling in line with annex 13 of the Rules Governing Medicinal Products in the European Union. This means the IMPs can be managed as normal, through a general practitioner or hospital prescription (as appropriate) and will not require special labelling, accountability, storage, etc.

#### Concomitant medication

Patients in all groups will have blood pressure controlled and total cholesterol lowered, using agents according to local unit guidelines and working to unit-defined targets. All other medication and treatment will be determined by local unit guidelines.

### Withdrawal of subjects

Individual recruits can withdraw at any time for any reason. Failure to tolerate one or more components of the treatment will definitely not be seen as a reason to withdraw an individual participant from the trial but is to be anticipated as an integral part of individualising therapy. Recruitment of new participants to the study will be halted temporarily on the advice of the data monitoring and ethics committee if any of the following are noted: a patient death attributable to treatment or an unacceptable incidence of severe adverse events attributable to treatment (if occurring in >10% of patients). In both these instances, the trial will undergo urgent review by the data monitoring and ethics committee and the trial steering committee.

The investigator has the right to withdraw patients from treatment with the study drug in the event of inter-current illnesses, adverse events, severe adverse events, suspected unexpected serious adverse reactions, protocol violations, cure, administrative reasons or other reasons. It is understood by all concerned that an excessive rate of withdrawals can render the study uninterpretable and unnecessary withdrawal of patients should be avoided. Should a patient decide to withdraw from the study, all efforts will be made to report the reason for withdrawal as thoroughly as possible. Should a patient withdraw from treatment with the study drug only, efforts will be made to obtain follow-up data, with the permission of the patient.

Participants who wish to withdraw from treatment will be asked to confirm whether they are still willing to provide study-specific data and samples for scientific laboratory analysis according to the trial protocol.

